### Data collection

PRIMIER currently uses the Research Electronic Data Capture (REDCap) system as an online research management tool to collect patient reported data. REDCap is a secure, web-based application designed exclusively to support data capture for research studies [12]. REDCap, which was initiated with funding from the National Institutes of Health, allows researchers to create study-specific websites for capturing participant data securely through an intuitive interface for users to enter data and have real time validation rules (with automated data type and range checks) at the time of entry. REDCap further allows automated data export procedures for seamless data downloads to Excel, SPSS, SAS, and Stata. Developed by Vanderbilt University, REDCap currently supports 994 academic/non-profit consortium partners and over 100,000 research end-users (http://project-redcap.org). From August 2013 to May 2015, PRIMIER patient surveys were collected using the Patient Reported Outcomes Measurement Information System (PROMIS) Assessment Center at Northwestern University. The database was changed to REDCap in May 2015 to give the BraveNet coordinating center (Albert Einstein College of Medicine) the ability to modify the survey and create one registry database instead of maintaining individual site databases as had been necessary with the Assessment Center platform.

### Data collection schedule

With the exception of the tobacco and alcohol use questionnaires and EHR data, all other data measures are collected seven times: at baseline and at two, four, six, 12, 18, and 24 months. Tobacco and alcohol use are asked at baseline, 12, and 24 months, and medical record data are pulled at baseline and every 6 months. See Table 2 for the schedule of data collection, and the following Demographics, Outcome Measures, and Utilization/Intervention Data sections for more detail.

**Table 2 Tab2:** Outcome Measures Utilized in PRIMIER

Measure	Frequency						
Demographics	Baseline	2 months	4 months	6 months	12 months	18 months	24 months
Age	●	●	●	●	●	●	●
Race	●	●	●	●	●	●	●
Ethnicity	●	●	●	●	●	●	●
Sex	●	●	●	●	●	●	●
Education	●	●	●	●	●	●	●
Marital status	●	●	●	●	●	●	●
Employment status	●	●	●	●	●	●	●
Insurance status	●	●	●	●	●	●	●
Likelihood of insurance billing	●	●	●	●	●	●	●
Household income	●	●	●	●	●	●	●
Self-reported height	●	●	●	●	●	●	●
Self-reported weight	●	●	●	●	●	●	●
Opioid medication use	●	●	●	●	●	●	●
Fruit and vegetable Intake	●	●	●	●	●	●	●
Tobacco and alcohol use	●				●		●
Exercise	●	●	●	●	●	●	●
Patient-Reported Outcome Measures							
PROMIS-29	●	●	●	●	●	●	●
PROMIS-1 (Quality of Life)	●	●	●	●	●	●	●
Perceived Stress Scale (PSS-4)	●	●	●	●	●	●	●
Patient Activation Measure (PAM)	●	●	●	●	●	●	●
Utilization/Intervention							
Patient Self-Report							
Experience with IM services	●	●	●	●	●	●	●
IM service utilization	●	●	●	●	●	●	●
Chronic pain	●	●	●	●	●	●	●
Primary condition being treated	●	●	●	●	●	●	●
Primary symptom being treated	●	●	●	●	●	●	●
Change in symptoms	●	●	●	●	●	●	●
Medical Records							
IM Clinic Visits							
Dates of all appointments to the IM clinic	●			●	●		●
IM services received	●			●	●		●
Diagnostic codes (ICD-9)	●			●	●		●
Billing codes (CPT)	●			●	●		●
Any Clinic Visit							
Height	●			●	●		●
Weight	●			●	●		●
Pain	●			●	●		●
Lipid Panels	●			●	●		●

### Demographics

PRIMIER participants are asked to answer 19 items relating to basic demographics: age, race, ethnicity, sex, education, marital, employment and insurance status, likelihood of insurance billing, household income, and self-reported height and weight. Lifestyle behaviors such as alcohol and tobacco use, nutrition and exercise habits, and use of opioid medication are also asked of all participants. These questions, shown in the Additional file 1, are not scored and will be treated categorically in data analyses.

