### Data analyses

#### General statistical considerations

All subjects who complete baseline measurements, ≥1 follow-up visit at a BraveNet clinic, and who are followed for at least 6 months in the study will be included in statistical analyses. Counts and percentages will be reported on categorical variables whereas continuous variables will be expressed as means and standard deviations (SDs) and/or medians (25^th^ and 75^th^ percentiles). The Wilcoxon rank-sum test or Chi-square test (Fisher’s exact as appropriate) will be used to quantify comparisons as deemed necessary.

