### Future data analysis

In observational studies like PRIMIER, there is no treatment randomization. Therefore, to minimize the effects of potential stable moderators (e.g., sex), channeling bias, and/or time- varying confounders, a Marginal Structural Model (MSM) approach will be utilized to analyze the final PRIMIER database. An MSM analysis is a weighted repeated measures approach using IM modality as a time-varying covariate as well as accounting for baseline characteristics. Weights produce a pseudo-population with a balance in both time-invariant and time-varying covariates, allowing for causal treatment comparisons using standard repeated measures models. The weighting will also be adjusted to account for missing data, providing validity under missing at random or missing completely at random. In order to incorporate adjustment for patients with missing visits, the same weight approach is used. However, instead of using a flag to designate IM modality, a flag denoting whether the patient remained in the study is used. The final weight for each patient’s observation is computed by multiplying the IM modality selection weights and the censoring weights. There are four major components which need to be computed/assessed to perform a MSM analysis: 1) weight estimates for each subject visit adjusting for IM modality, 2) weight estimates for each subject visit adjusting for study discontinuation, 3) an a priori chosen vector of time-independent variables, such as baseline characteristics, 4) an a priori chosen IM modality or set of IM modalities which will be assigned as the “treatment of interest” and tracked throughout time. Adjusted mean outcomes by study time as well as resulting F-test p-values will be reported by outcome measure.

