As our sample size increases and the proportion of those completing long term follow-up assessments grows, we will be able to evaluate the impact of IM on pain scores in subgroups including but not limited to: sex, BMI < 30 vs BMI ≥ 30, and <40 on the PROMIS Depression Subscale vs ≥40 on PROMIS Depression Subscale. The potential of the varying impacts of IM on subgroups will be assessed by including interaction terms, i.e., subgroup by IM, in the MSM model. In the case that the interaction terms are statistically significant, separate MSM analyses will be performed within each subgroup. Also, the weight estimates for each subject visit will be computed adjusting for dose of modality or modalities of interest (e.g., acupuncture or IM physician visit) instead of IM modality in the MSM analysis. Accounting for modality dosing by visit over the course of the study may potentially create more robust weight estimates for each subject by providing more information than just a binary response variable.

Sensitivity analysis to assess the impact of retention rate will be performed on pre-specified subgroups of subjects who completed:75 % of surveys over the study period50 % of surveys over the study period25 % of surveys over the study period

All analyses will be conducted using SAS (Cary, NC).

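### Treating age and body size as categories, and testing effect modification through two-way cuts of BMI and depression score, discards information that continuous terms would keep

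*Protocol article*

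**What the plan says.** The Demographics section of the protocol article names the baseline items. They include age and, at the end of the list, "likelihood of insurance billing, household income, and self-reported height and weight". It then adds lifestyle items (alcohol, tobacco, nutrition, exercise, opioid use) and states that the questions "are not scored and will be treated categorically in data analyses". The sentence is not limited to descriptive tables. The wording of the questions is in an additional file that is not shown, so the number and limits of any categories are unknown.

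Under General statistical considerations, "continuous variables will be expressed as means and standard deviations (SDs) and/or medians", so the plan expects some variables to stay continuous.

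Under Future data analysis, confounding is handled by an MSM. "Weights produce a pseudo-population with a balance in both time-invariant and time-varying covariates", and the model also uses "an a priori chosen vector of time-independent variables, such as baseline characteristics". Neither the covariates nor their coding are listed.

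The same section examines the effect of integrative medicine on pain scores in an open-ended list of subgroups that names "sex, BMI < 30 vs BMI ≥ 30, and <40 on the PROMIS Depression Subscale" against 40 or more. Effect modification is tested by a subgroup-by-treatment interaction in the MSM. Separate models within subgroups follow only if that interaction is significant.

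**The concern.** There are two issues, and they rest on different parts of the article.

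**Confounding.** The registry is not randomised, so its comparisons of modalities depend on the weights balancing baseline covariates. Weights built on bands balance the bands, not the values inside them. If older patients within an age band choose a modality more often, that difference stays. It is a bias and not a variance, so it does not shrink as enrolment grows.

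**Power for effect modification.** Cutting a continuous modifier in two discards the ordering on each side of the cut. If the effect changes steadily with BMI or depression score, the interaction test is weaker than one on the score itself. That test also decides whether the within-subgroup models are run, so a missed interaction carries through.

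The article accepts the same principle elsewhere. Under Future data analysis it proposes weights based on the dose of a modality, because dose carries more information than a binary indicator.

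**Working it through.** The article gives no significance level, power, effect size or standard deviation for these analyses, so there is no planned figure to reproduce. Apart from the anticipated enrolment of about 10,000 (Screening procedures and enrollment), every input below is an assumption made for illustration.

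**1. Bias left by banding.** Assume one standard normal confounder with a linear effect, split into k equal-sized bands. The share of its bias removed is the between-band variance, the mean of the squared band means; the share left is 1 minus that.

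- k = 2: band means ±0.798; 0.798² = 0.637 removed, 0.363 left.
- k = 3: outer band means ±1.091, middle 0; (2/3) × 1.091² = 0.793 removed, 0.207 left.
- k = 4: 0.861 removed, 0.139 left.
- k = 5: 0.897 removed, 0.103 left.
- k = 10: 0.959 removed, 0.041 left.

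**2. Check by simulated inverse-probability weighting.** This used a single time point, n = 400,000, true treatment effect 0 and an outcome slope of 0.3 per SD of the confounder.

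| Treatment log-odds per SD | Crude bias | 2 bands | 3 | 4 | 5 | 8 | Continuous |
|---|---|---|---|---|---|---|---|
| 0.5 | 0.142 | 37.3% left | 21.1% | 14.4% | 10.6% | 6.2% | 0.0009 (under 1%) |
| 1.0 | 0.249 | 37.8% left | 21.6% | 15.5% | 11.7% | 6.7% | 0.0014 (under 1%) |

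The simulation agrees closely with step 1. It does not reproduce the longitudinal weights of the plan.

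**3. Information kept by a two-way cut.** For a standard normal modifier with a linear interaction, cut at c with a share p above it, the information kept is φ(c)² / [p(1 − p)], where φ is the normal density. If the continuous test has 80% power at two-sided 0.05, the power after the cut is Φ[(1.960 + 0.842) × √(information kept) − 1.960].

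| Share above the cut | Information kept | Power, against 80% continuous |
|---|---|---|
| 50% | 0.3989² / 0.25 = 0.637 | 61% |
| 30% | 0.3477² / 0.21 = 0.576 | 57% |
| 20% | 0.490 | 50% |
| 10% | 0.342 | 37% |

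The article does not give the share of patients above BMI 30 or on either side of 40 on the depression score.

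**4. Whether the loss matters.** Assume residual SD 1 and half the patients treated. The standard error of the interaction per SD of modifier is 1 / √(N × 0.25), which is 0.020 at N = 10,000.

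| N | Interaction per SD of modifier | Continuous | Median split | 30:70 cut |
|---|---|---|---|---|
| 10,000 | 0.10 SD | 99.9% | 97.9% | 96.7% |
| 10,000 | 0.05 SD | 70.5% | 51.4% | 47.5% |
| 2,000 | 0.10 SD | 60.9% | 43.0% | 39.6% |

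The smaller N is relevant because the article plans analyses in specific clinical populations and for specific interventions (Abstract). It also limits analysis to patients with baseline data, at least one follow-up visit and at least 6 months of follow-up (General statistical considerations).

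**The case against.** The strongest reply is that the Demographics sentence may only separate unscored questionnaire items from the scored instruments described next, and that it follows directly on the lifestyle items. The functional form of model covariates is commonly left to the analysis plan, which is not shown. This stands in part: a reader might infer that age and BMI will be banded in the weights, but the article does not say so, and the confounding point is therefore conditional. What remains is a stated rule for data analyses in general, in a paragraph that names age, height and weight.

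A reader might also infer that the rule contradicts the BMI subgroup, since BMI needs numeric height and weight. This is not established. Table 2 and the Utilization/intervention data section list height and weight from medical records, and BMI could come from there.

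Income may have been asked in bands. Treating it as categories would then lose nothing at the analysis stage.

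On the cuts, three replies have force. The subgroup list is open-ended and does not exclude continuous modifiers. A subgroup contrast estimates an average effect in each group and does not assume that the effect is constant within it; it also gives results that are easy to report. The efficiency loss applies to a linear interaction and can reverse if the effect changes at a threshold. None of this restores the information lost when the effect varies smoothly.

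Finally, the categorical rule does not govern PROMIS Depression, which is a scored instrument. The criticism of that cut rests on the Future data analysis section alone.

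**Conclusion.** The point holds as a conditional weakness on confounding and a firmer one on the interaction test.

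- **Confounding:** if numeric age or body size is banded in the weight or outcome models, some of its bias remains at any sample size. The illustrative range is about 36% with 2 bands to 10% with 5, assuming one normal confounder, a linear effect and equal-sized bands. The actual number of bands is unknown, and the remainder is modest with five or more.
- **Interaction test:** the cuts are written into the plan. For a linear interaction with a normal modifier they keep at most about 64% of the information, and less for unequal splits.

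A reader might conclude that 10,000 patients are reduced to about 6,400 (10,000 × 0.637) and that the subgroup analyses are therefore inadequate. The documents do not support that. Under the assumptions above, a 0.10 SD interaction at the full 10,000 loses only about 2 percentage points of power with a median split. The loss becomes material, near 18 to 19 points, for a 0.05 SD interaction at 10,000 or a 0.10 SD interaction at 2,000. The article gives neither the expected interaction nor the number retained. The change is worth making because it costs little, not because the plan fails without it.

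**What to change.** 1. **Demographics:** limit the sentence to items recorded as categories. Items collected in bands, such as income if it was so collected, stay as they are.
2. **Weight and outcome models:** state that age and BMI, where recorded as numbers, enter as continuous terms, for example restricted cubic splines.
3. **Effect modification:** test the interactions with continuous BMI and continuous baseline PROMIS Depression score. Keep the stated cut-points for presenting subgroup estimates. Sex is already binary and needs no change.

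The cost is a few changed sentences, slightly more model coding and a less direct presentation of the interaction. No new data are needed where the items are stored as numbers.

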### Patient-reported outcome measures

PRIMIER uses the PROMIS-29 instrument as the core PRO measure along with the Perceived Stress Scale-4 (PSS-4) [13] and the Patient Activation Measure (PAM) [14].

Created with funding from the National Institutes of Health, the PROMIS suite of PRO instruments provides clinicians and researchers access to efficient, valid, and responsive self-reported measures of health, including symptoms, function, and well-being. The PROMIS-29 instrument includes four-item short forms covering seven distinct domains including physical function, anxiety, depression, fatigue, pain intensity and pain interference, satisfaction with social role, as well as sleep disturbance. Questions are answered using standard one through five Likert scales. The PROMIS-29 has been validated as performing as well as a variety of legacy PRO measures [15], and the four-item subscales for depression and anxiety have been found to have good internal reliability among chronic pain patients [16]. A crosswalk has been developed and validated between PROMIS Pain Interference and the Pain Interference subscale of the Brief Pain Inventory [17], and between the PROMIS Fatigue short form and the Modified Fatigue Impact Scale [18]. PROMIS Depression has also been cross-walked with several common depression measures (e.g., Beck Depression Inventory-II and Center for Epidemiologic Study-Depression) [19]. In addition to the PROMIS-29, we include one PROMIS question to assess global quality of life.

The Perceived Stress Scale-4 (PSS-4) is a brief, validated, and widely used psychological instrument for assessing a participant’s perception of stress level. Based on an original 14-item scale [20], the PSS-4 consists of four questions to measure the degree to which participants perceive situations in their lives as stressful [13]. It includes questions related to perceived unpredictability, uncontrollability, and overload. This short version is recommended for a brief assessment when respondent time is limited. Participants choose responses ranging from never (0) to very often (4) with a total score ranging from 0 to 16. A recent study on the PSS-4 reconfirms its reliability [21].

The Patient Activation Measure (PAM) is a brief, validated instrument for gauging the knowledge, skills and confidence essential to managing one’s own health and healthcare [14]. The 13-item PAM assessment (a short form of the original 22-item instrument) [22] divides participants into one of four progressively higher activation levels. Each level addresses a broad array of self-care behaviors and offers insight into the characteristics that drive health activation [22]. Positive changes in activation have been associated with positive changes in a variety of self-management behaviors [23]. Improvement in patient activation has been shown to be strongly related to improvements in clinical outcomes such as decreased pain, increased utilization of prevention screenings, and a reduction in emergency room visits [23]. The four levels are defined as: Level 1 – Does not believe that he/she has an active or important role; Level 2 – Lacks confidence and knowledge to take action; Level 3 – Beginning to take action; and Level 4 – Maintaining behavior over time. The PAM has been used in several studies of IM interventions [24–26].

### Utilization/intervention data

In addition to providing PRO measures, participants report the primary condition(s) or symptom(s) for which they are receiving treatment and the type of IM practitioner from whom they are receiving care based on questions from the National Health Interview Survey. At each data collection point, patients are asked to rate or describe their change in symptoms, etc. since beginning care at the IM clinic [27]. Patients report whether they are experiencing chronic pain, defined as 4 or greater on an 11-point visual analog scale. PRIMIER also collects information on what IM interventions patients have utilized in the past 6 months. Utilization of IM treatments is captured through two methods: 1) as reported by the study participants using patient visit questionnaires; and 2) as reported by the sites through an electronic or paper medical record extraction process. Each site abstracts the following data points from their participant’s electronic medical and administrative records: dates of all appointments to the IM clinic, IM services received, diagnostic codes (International Classification of Diseases-9: ICD-9) associated with each IM visit, and billing codes (Current Procedural Terminology: CPT) associated with each visit. These data are encrypted and sent electronically to the BraveNet data coordinating center. Additional data fields will be added from patient visits to any clinic (i.e., not limited to IM clinic visits) as relevant to specific studies of interest, for example, height, weight, pain, and lipid panels.

### Data analyses

#### General statistical considerations

All subjects who complete baseline measurements, ≥1 follow-up visit at a BraveNet clinic, and who are followed for at least 6 months in the study will be included in statistical analyses. Counts and percentages will be reported on categorical variables whereas continuous variables will be expressed as means and standard deviations (SDs) and/or medians (25^th^ and 75^th^ percentiles). The Wilcoxon rank-sum test or Chi-square test (Fisher’s exact as appropriate) will be used to quantify comparisons as deemed necessary.

### Future data analysis

In observational studies like PRIMIER, there is no treatment randomization. Therefore, to minimize the effects of potential stable moderators (e.g., sex), channeling bias, and/or time- varying confounders, a Marginal Structural Model (MSM) approach will be utilized to analyze the final PRIMIER database. An MSM analysis is a weighted repeated measures approach using IM modality as a time-varying covariate as well as accounting for baseline characteristics. Weights produce a pseudo-population with a balance in both time-invariant and time-varying covariates, allowing for causal treatment comparisons using standard repeated measures models. The weighting will also be adjusted to account for missing data, providing validity under missing at random or missing completely at random. In order to incorporate adjustment for patients with missing visits, the same weight approach is used. However, instead of using a flag to designate IM modality, a flag denoting whether the patient remained in the study is used. The final weight for each patient’s observation is computed by multiplying the IM modality selection weights and the censoring weights. There are four major components which need to be computed/assessed to perform a MSM analysis: 1) weight estimates for each subject visit adjusting for IM modality, 2) weight estimates for each subject visit adjusting for study discontinuation, 3) an a priori chosen vector of time-independent variables, such as baseline characteristics, 4) an a priori chosen IM modality or set of IM modalities which will be assigned as the “treatment of interest” and tracked throughout time. Adjusted mean outcomes by study time as well as resulting F-test p-values will be reported by outcome measure.

As our sample size increases and the proportion of those completing long term follow-up assessments grows, we will be able to evaluate the impact of IM on pain scores in subgroups including but not limited to: sex, BMI < 30 vs BMI ≥ 30, and <40 on the PROMIS Depression Subscale vs ≥40 on PROMIS Depression Subscale. The potential of the varying impacts of IM on subgroups will be assessed by including interaction terms, i.e., subgroup by IM, in the MSM model. In the case that the interaction terms are statistically significant, separate MSM analyses will be performed within each subgroup. Also, the weight estimates for each subject visit will be computed adjusting for dose of modality or modalities of interest (e.g., acupuncture or IM physician visit) instead of IM modality in the MSM analysis. Accounting for modality dosing by visit over the course of the study may potentially create more robust weight estimates for each subject by providing more information than just a binary response variable.

Sensitivity analysis to assess the impact of retention rate will be performed on pre-specified subgroups of subjects who completed:75 % of surveys over the study period50 % of surveys over the study period25 % of surveys over the study period

All analyses will be conducted using SAS (Cary, NC).

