### Screening procedures and enrollment

Potential participants receive PRIMIER enrollment information either from clinic or research staff. Patients who decide to participate in PRIMIER log onto the PRIMIER website and electronically enroll directly into the registry. Online registrants are able to provide informed consent upon opening the first screen on their initial visit to the website. If they do not have computer access or are uncomfortable with technology, patients may provide informed consent and complete the survey questionnaire by pen and paper. Following enrollment in PRIMIER, PRO measures are obtained at 2-month intervals for the first 6 months, then every 6 months through the end of year two. This information is combined with data extracted from the participants’ EHR. We anticipate approximately 10,000 participants to be enrolled in PRIMIER.

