From our prior mapping study of IM in the United States [31], and from a BraveNet Registry study [28–30], we learned that IM center leaders across the country perceived that their interventions were most useful in patients with complaints of chronic pain, depression, and stress. In a different study of patients with a chief complaint of chronic pain seen at the BraveNet sites, we previously reported that an IM approach to pain not only decreased pain, but depressive symptomology and stress as well [29]. Both of these studies were limited by virtue of either one-time only assessment [28–30] or small sample size [29]. From a more mature PRIMIER dataset, we should be able to ascertain which particular treatment modalities offer the greatest reduction in pain, as well as changes on measures of depressive symptomology and stress as examples.

The PRIMIER project offers a unique opportunity to assess the effectiveness of IM clinic intervention in a wide variety of clinical conditions. As the dataset grows and the duration of follow-up increases, we expect to be able to derive preliminary information to develop specific research proposals to address the difficult- to-treat conditions for which patients seek our care.

Given the rapid increase in the number of clinical settings offering IM services, the public is continuing to seek out these therapies to augment and integrate with conventional medical practices. While randomized controlled trials assess the efficacy of specific interventions for specific patient populations in “controlled settings”, observational studies evaluate the effectiveness of treatments in the real world of clinical practice. The highly individualized nature of IM interventions also can make the randomized controlled trials model problematic, since treatments often evolve over time as a function of a given individual’s response to treatment. Although there is now a growing body of randomized controlled trial research on the efficacy of integrative medicine approaches for a variety of conditions [32–38], in many ways this body of research does not accurately describe the real world practice of IM because of the controlled nature of the clinical trial paradigm. In contrast, observational research designs, despite some inherent limitations, present a promising option. Bell et al. suggest that observational designs are appropriate for studying complex interventions, despite the absence of randomization [2].

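### Weighting alone does not make every standard repeated-measures model valid: a correlated fit biases the modality contrast, and model-based standard errors can separately inflate the error rate

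*Protocol article*

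**What the plan says.** All of the method is in the Protocol article, section Future data analysis. The weighting is introduced "to minimize the effects of potential stable moderators (e.g., sex), channeling bias, and/or time- varying confounders". The model is described in one sentence: "An MSM analysis is a weighted repeated measures approach using IM modality as a time-varying covariate as well as accounting for baseline characteristics". Each visit has its own weight: "The final weight for each patient’s observation is computed by multiplying the IM modality selection weights and the censoring weights". The article then draws the inference at issue, that the weights balance the sample, "allowing for causal treatment comparisons using standard repeated measures models". On reporting it says: "Adjusted mean outcomes by study time as well as resulting F-test p-values will be reported by outcome measure". The section adds that SAS will be used.

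Three other places set the conditions. The Discussion says that in integrative medicine "treatments often evolve over time as a function of a given individual’s response to treatment". Under Data collection schedule the outcome measures are "collected seven times: at baseline and at two, four, six, 12, 18, and 24 months". Under Screening procedures and enrollment: "We anticipate approximately 10,000 participants to be enrolled in PRIMIER".

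The article names no working correlation, random effects, variance estimator, SAS procedure or significance level.

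**The concern.** This is a stated principle, not only a missing detail. It tells the analyst that once the weights are computed, any ordinary repeated-measures model gives a causal contrast. For a time-varying treatment with visit-specific weights that holds for some such models and fails for others. The ones that fail include the mixed or exchangeable model that many analysts would reach for first.

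The condition that makes it fail is the one the authors describe: treatment that adapts to earlier response. At stake is the analysis planned for the final registry database. A significant subgroup interaction in the same model also triggers separate subgroup analyses, so errors in its tests carry forward.

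**Working it through.** **There is no figure to reproduce.** The article gives no alpha, SD, within-patient correlation or effect size, and the 10,000 is an anticipated enrolment. The check is therefore algebra followed by simulation.

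**Step 1: why the working correlation matters.** The weighted estimating equation sums, over patients and over pairs of visits (s, t), terms of the form

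x(s) × v(s,t) × w(t) × [Y(t) − μ(t)],

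where x(s) is the covariate row at visit s (including modality), v(s,t) is an element of the inverse working correlation and w(t) is the weight at visit t. That weight accounts for modality choices up to visit t only. If v(s,t) is not zero for s later than t, the residual at t is paired with a later modality that was chosen partly because of Y(t). The expectation of that term is not zero even when modality has no effect. Under independence, v(s,t) = 0 for s ≠ t and these terms vanish.

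They are not negligible. With 6 follow-ups and the residual correlation of about 0.37 seen in the simulations:
- ρ / (1 + 5ρ) = 0.37 / 2.85 = 0.130, and 1 / (1 − ρ) = 1.587
- diagonal element: 1.587 × (1 − 0.130) = 1.38
- off-diagonal element: −1.587 × 0.130 = −0.206

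Each off-diagonal is about 15% of the diagonal, and it is negative. If a higher score makes the modality more likely, the bias should be negative.

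**Step 2: simulation under a true null.** From the article: one baseline and six follow-ups; modality dependent on the previous outcome. Assumed: outcome SD 1; intra-patient correlation 0.6; feedback of 0.25 or 0.5 log-odds per SD of the previous outcome; persistence of modality of 1 or 3 log-odds; two-sided 5% test. Stabilised weights came from a correctly specified model, without truncation. The outcome model had visit effects, baseline outcome and current modality. There were 120 to 500 replicates, so the Monte Carlo SE near 5% is about 1 to 2 percentage points.

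| n | feedback | persistence | Independence: bias (SD) | reject, sandwich | reject, model-based | Exchangeable: bias (SD) | reject, sandwich | reject, model-based |
|---|---|---|---|---|---|---|---|---|
| 500 | 0.25 | 3 | +0.002 | 5.0% | 13.0% | −0.026 | 15.4% | 15.8% |
| 2,000 | 0.25 | 3 | −0.001 | 3.5% | 12.2% | −0.029 | 47.2% | 47.7% |
| 2,000 | 0.5 | 1 | −0.001 | 4.5% | 10.2% | −0.042 | 82.3% | 84.3% |
| 2,000 | 0.5 | 3 | +0.001 | 3.0% | 11.7% | −0.054 | 89.0% | 91.7% |
| 10,000 | 0.25 | 3 | −0.001 | 1.7% | 7.5% | −0.029 | 99.2% | 99.2% |
| 10,000 | 0.5 | 1 | 0.000 | 2.5% | 6.7% | −0.042 | 100% | 100% |

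With cumulative rather than current modality (n=2,000, feedback 0.25, persistence 3), the independence fit rejected 16.8% with model-based and 3.5% with sandwich SEs.

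A second set of null simulations over the same feedback range gave −0.02 to −0.04 SD for the exchangeable fit, with rejection of 14-34%, 30-80% and 88-100% at the three sample sizes. The combined ranges in the verdict cover both sets.

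**Step 3: the rates follow from the bias.** For n=2,000, feedback 0.5, persistence 1, the exchangeable fit has bias 0.0419, empirical SE 0.0154 and sandwich SE 0.0141. Expected rejection is Φ[(0.0419 − 1.96 × 0.0141) / 0.0154] = Φ(0.93) ≈ 0.82, as observed. The sandwich SE is roughly right; it is the estimate that is off centre. The bias stays near 0.03 to 0.04 SD as n grows while the SE shrinks, so rejection approaches 100%.

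**Step 4: weak or no feedback.** At log-odds 0.1 and n=2,000, with weights truncated at the 1st and 99th percentiles, the exchangeable bias is −0.009 SD and rejection 11%. Over the runs at this strength the rates are about 5-6% at n=500, 9-11% at n=2,000 and 32-35% at n=10,000. With no feedback, every version rejects about 4 to 6% and none is biased.

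**The case against.** The strongest reply is that the article does not prescribe the model that fails. A weighted fit with independence working correlation and sandwich variance is itself a repeated-measures analysis, is available in SAS, fits the article's words and performs well above. F-tests can be built on a sandwich variance, so that wording does not settle the matter. A condensed article may leave the covariance structure and variance estimator to the analysis plan, and their absence is no finding.

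All of that stands. It makes the point conditional but does not remove it, because the sentence asserts a sufficiency that is untrue for a common class of models.

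A reader might infer more: that the registry's final analysis is bound to be biased, with error rates far above 5% at any sample size. The documents do not support that. It would require a correlated or model-based fit that is nowhere stated, and a feedback strength that the article describes only in words.

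A reader might also object that adjusted means with p-values give no effect estimate, or that at 10,000 patients trivial differences become significant. The first is overstated: if means are given by modality, their differences are the estimate. The second applies to any test at that size, including the one proposed below. Both are reporting preferences.

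**Conclusion.** The sentence is too broad and should be corrected; whether the planned analysis is wrong depends on what *standard* turns out to mean. Two separate problems should not be merged.

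- **Correlated working structure.** With feedback of log-odds 0.25 to 0.5 per SD, the null contrast is biased by about 0.02 to 0.05 SD (0.2 to 0.5 points if the SD is 10, which the article does not state). False-positive rates are about 14-34% at n=500, 30-92% at n=2,000 and 88-100% at n=10,000. Sandwich SEs do not repair this. The bias is small in absolute terms; the very high rates arise because a fixed small bias meets a large sample.
- **Independence structure with model-based SEs.** No bias, but rejection of about 7% to 17%.

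These sizes rest on the assumed feedback, correlation, persistence and 5% level. The direction of the finding rests only on the article's own statement that treatment adapts to response.

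**What to change.** Replace the sentence on standard repeated-measures models. Say that the weighted outcome model is fitted by estimating equations with an independence working correlation, stabilised weights and participant-clustered sandwich variance (or a participant-level bootstrap that re-estimates the weights). Base the F-tests on that variance, and report modality contrasts with 95% CIs beside the adjusted means.

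Any truncation of the weights should be stated too. With truncation at the 1st and 99th percentiles and feedback of 0.25 to 0.5, the independence fit kept a residual bias of about 0.003 to 0.010 SD, and rejected 9% to 14% at n=10,000 even with sandwich SEs.

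The cost is wording and somewhat wider intervals. At n=2,000 the sandwich SE under independence was 0.0174 to 0.0215, against 0.0132 to 0.0156 for the model-based SE of the exchangeable fit, a ratio of about 1.3 to 1.4. No new data are needed.
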